### Participant Timeline

Patients will be assessed at baseline and after 3, 6, 12, and 24 months. At each visit, patients will fill out online questionnaires (~30 min) and are assessed by the RN, who calculates the DAS28 or DAPSA depending on the diagnosis. Study visits will take 30 minutes or less. The timeline and extensive data collection overview are shown in Figure 2 and Table 2. Data collection is the same for both the intervention group and the control group.

**Figure 2. F2:**
[figure not shown]
Participant timeline.

**Table 2. T2:** Overview of data collection in intervention and control groups.

Data collection	T0	T3	T6	T12	T24
In-hospital evaluation					
Diagnosis: RA^a^ or PsA^b^	✓				
Check other inclusion and exclusion criteria	✓				
Informed consent	✓				
Demographic	✓				
History (fulfillment ACR^c^/and EULAR^d^ criteria for RA and PsA, disease duration, auto-antibody status, presence of erosions, DMARD^e^ history)	✓				
Comorbidity	✓				
Global assessment of disease activity by patient and RN^f^	✓	✓	✓	✓	✓
Adverse events (self-reported)		✓	✓	✓	✓
Hospital admission		✓	✓	✓	✓
Length, Weight, BMI, and waist circumference	✓	✓	✓	✓	✓
Physical examination by RN	✓	✓	✓	✓	✓
Online questionnaires					
General (smoking, alcohol, and drugs)	✓				
General health (VAS^g^)	✓	✓	✓	✓	✓
Pain (VAS)	✓	✓	✓	✓	✓
Morning stiffness (severity and duration; NRS^h^)	✓	✓	✓	✓	✓
Fatigue (VAS and FACIT-F^i^)	✓	✓	✓	✓	✓
HAQ^j^ (functional ability)	✓	✓	✓	✓	✓
EQ-5D-5L (quality of life)	✓	✓	✓	✓	✓
SF-36^k^ (quality of life)	✓			✓	✓
RAPID-3^l^	✓	✓	✓	✓	✓
Sleep (MOS-SS^m^)	✓	✓	✓	✓	✓
Perceived stress	✓	✓	✓	✓	✓
Physical activity	✓	✓	✓	✓	✓
Diet compliance	✓	✓	✓	✓	✓
WPAI^n^ (work and productivity)	✓	✓	✓	✓	✓
Medical consumption (MCQ^o^)	✓	✓	✓	✓	✓
Total time (min)	~34	~30	~30	~34	~34
Routine laboratory tests	✓	✓	✓	✓	✓

a RA: rheumatoid arthritis.

b PsA: psoriatic arthritis.

c ACR: American College of Rheumatology.

d EULAR: European Alliance of Associations for Rheumatology.

e DMARD: disease-modifying antirheumatic drug.

f RN: research nurse.

g VAS: Visual Analog Scale.

h NRS: Numeric Rating Scale.

i FACIT-F: Functional Assessment of Chronic Illness Therapy-Fatigue.

j HAQ: Health Assessment Questionnaire.

k SF-36: 36-item Short Form Health Survey.

l RAPID-3: Routine Assessment of Patient Index Data 3.

m MOS-SS: Medical Outcomes Study sleep scale.

n WPAI: Work Productivity and Activity Impairment.

o MCQ: Medical Consumption Questionnaire.

### Primary End Point

The primary objective is the proportional difference in DAS28 and DAPSA remission and/or successful tapering of DMARD treatment after 12 months of follow-up. Meeting either criterion is sufficient to qualify for the primary outcome.

Disease activity in patients with RA and PsA is measured with the DAS28 and DAPSA, respectively [23,24]. The DAS28 is a pooled index that involves the incorporation of a 28-joint count for tenderness (TJC28), a 28-joint count for swelling (SJC28), an erythrocyte sedimentation rate (ESR) and GH (measured with a Visual Analog Scale [VAS] 0‐100 mm) into a formula to obtain a numerical indicator of disease activity. The DAS28 formula is 0.56√(TJC28)+0.28√(SJC28)+0.70ln(ESR)+0.014(GH) [23]. The DAPSA is also a pooled index, which is made up of the following five domains: (1) a 68-joint count for tenderness, (2) a 66-joint count for swelling, (3) a CRP (expressed in mg/dL), (4) a patient’s assessment of the disease activity (VAS, 0‐10 cm), and (5) a patient’s assessment of pain severity (VAS, 0‐10 cm). The numerical values of the aforementioned 5 domains are summed to provide the DAPSA score [24]. The threshold values for DAS28 and DAPSA remission are <2.6 and ≤4, respectively [24,26]. The minimal clinically important differences (MCIDs) for the change in DAS28 and DAPSA are 1.2 and 7.2, respectively [27,28]. Tapering of treatment is left to the discretion of the treating rheumatologist in consultation with the patient, with current treatment recommendations as a guideline.

### Secondary End Points

Secondary end points include cost-effectiveness, health risk, and (self-reported) disease burden (refer to Table S1 in Multimedia Appendix 1). Cost-effectiveness will be evaluated through the ICER, which is the ratio of the difference in costs to incremental benefits between the online interactive lifestyle intervention program and general nutrition recommendations. For the cost-effectiveness analysis, we will calculate the quality-adjusted life years (QALYs) and total costs. QALYs express the impact of the disease on patients’ health over time. Living in perfect health corresponds to a QALY of 1 and a QALY of 0 reflects death [29]. QALYs are determined by calculating the area under the curve of the EQ-5D-5L [30]. Costs are divided into direct and indirect costs. We will analyze direct and indirect costs from a societal perspective. Direct costs are the costs of treatment and medical consumption, whereas indirect costs are costs due to loss of productivity [31]. Medication costs are calculated from doses reported in the patients’ case records, valued according to the Dutch National Health Care Institute [32]. Medical consumption, including duration of hospitalizations and admission diagnosis, are recorded every 3 months with the Institute for Medical Technology Assessment medical consumption questionnaire. We will use the Dutch average length of stay by diagnosis if the duration of hospitalization is unknown. Indirect costs include not fully functioning (presenteeism), sick leave (absenteeism), and reduction in work time [33]. Work Productivity and Activity Impairment (WPAI) outcomes are expressed as impairment percentages, with higher numbers indicating greater impairment and less productivity.

The health risk is assessed by measuring weight, BMI, and waist circumference. BMI is calculated by dividing the patient’s weight (kg) by the square of their height (m). A BMI ranging from 18.5 to <25 is classified as a healthy weight. A BMI between 25 and <30 is categorized as overweight, while a BMI ≥30 is considered obese. Conversely, a BMI <18.5 is classified as underweight [34]. Sex-specific thresholds for waist circumference are associated with an elevated risk of metabolic complications. In males, a waist circumference ≥94 cm is linked to an increased risk, whereas a measurement of ≥102 cm corresponds to a substantially increased risk. For females, these thresholds are ≥80 cm and ≥88 cm, respectively [34].

Disease burden is measured through the following PRO measurements: GH, pain, morning stiffness, fatigue, functional ability, and quality of life. GH, fatigue, and pain are measured with a VAS (0‐100 mm), whereby higher scores reflect greater severity. The MCIDs for the aforementioned outcomes are ≥10 [35-37]. Fatigue is also measured with the Functional Assessment of Chronic Illness Therapy-Fatigue questionnaire (FACIT-F) [38]. The FACIT-F consists of 13-items with a 7-day recall period. Items are scored on a 0‐4 response scale with anchors ranging from “Not at all” to “Very much so.” All items are summed to create a single fatigue score with a range from 0 to 52 and higher scores represent less fatigue [38]. The MCID is 15.9 [39]. Morning stiffness (severity and duration in min) is measured with a Numeric Rating Scale and is interpreted similarly to GH. The MCID for morning stiffness is ≥1 [40]. Functional ability is measured with the Health Assessment Questionnaire [41]. Higher Health Assessment Questionnaire scores indicate poorer function, and the MCID is 0.22 [41,42].

Quality of life is measured with the EQ-5D-5L (MCID ≥0.04) [43,44]. Higher scores represent a higher quality of life. We will also use the 36-item Short-Form Health Survey (SF-36) that assesses 8 domains on a scale of 0‐100, with higher scores indicating a better health status [45]. The SF-36 addresses the following domains: physical functioning, bodily pain, role limitations due to physical health problems and social or emotional problems, mental health, vitality, and GH perceptions. These domains are also combined into a physical and mental component score. The MCIDs for the physical component score and mental component score are 2.5 and 5, respectively [30,45,46].

Although the primary outcome will be assessed after 12 months of follow-up, we will follow all participants for 2 years to determine the long-term effect of the lifestyle intervention and whether the intervention has led to a permanent behavioral change.

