### Interventions

#### Online, Interactive Lifestyle Intervention Program

The online, interactive lifestyle intervention program (Leef! met Reuma) consists of a 6-month, intensive part followed by an 18-month online aftercare period. The online program focuses on 4 pillars, namely nutrition, exercise, relaxation, and sleep. The general principles for each pillar are summarized in Table 1. All principles are explained in more detail during the online plenary sessions (the why and how behind them) through Zoom (Zoom Communications Inc), which can be accessed via a standard web browser. Participants are given tools to implement a healthier lifestyle and to increase their health skills. They are encouraged to implement those changes in ways that fit their daily life. The lifestyle intervention aims for lasting behavior changes (based on the I-Change model) [18]. The guidance team consists of a coach, a dietitian, a program coordinator, and experts on sleep, relaxation, and physical activity. The nutritional advice and diet recommended throughout the course are based on the Dutch Health Council guidelines and existing scientific literature. The diet that is prescribed is comparable to the Mediterranean diet, with an emphasis on unprocessed foods (especially vegetables) and 3 meals a day. Alcohol is excluded from the diet.

Each month, a different pillar is highlighted. Throughout the month, participants are assigned 10 days of daily tasks focused on physical activity, relaxation, or sleep (with the option to extend this period to 28 d). Figure 1 provides a schematic overview of the intervention.

**Table 1. T1:** General principles of Leef! met Reuma.

Pillar	Principles
Nutrition^a^	Eat unprocessed foods and vary in the foods you eat. Eat mostly plant-based. Pay attention to dietary quality and not solely energy content.
Physical activity	Strive to increase your heart rate with moderate-intense physical activity for at least 15‐30 min a day. Implement more physical activity during the day; all physical activity counts. Vary in the type of physical activity you do and find a type of physical activity that suits you and that you can enjoy.
Relaxation	Learn to notice when you are stressed and what causes you to be stressed. Find your personal way to implement relaxation. Control your breathing.
Sleep	Pay special attention to sleep quality and not only to the amount of sleep. Develop your own personal, effective sleep hygiene.

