**Figure 1. F1:**
[figure not shown]
Schematic overview intervention (Leef! met Reuma).

There are 5 online plenary sessions lasting 3 to 4 hours for all participants (50 per group), and each session focuses on 1‐2 pillars. The online sessions start with a presentation with in-depth information about the specific pillar, and throughout the presentation, participants can ask questions. After that, the group is divided into several smaller online coaching groups. In these groups, the coach explains how to implement specific changes into participants’ lifestyles. During these 1-hour coaching sessions, the progress that participants have made will be discussed, but also obstacles, experiences, or situations that participants have encountered. Tips are given to help them stay motivated and keep the lifestyle behavioral changes they have made. One example is that participants will learn how to develop their own recipes according to the nutrition principles of the lifestyle program.

After the first 6 months, participants can participate in facultative sessions to stay motivated and foster the healthier habits they have learned during the intensive part of the program. These facultative sessions are similar to the coaching sessions but also include a recap of the knowledge gained during the first 6 months of the program. A facultative session is organized every 9 weeks. The total duration of these plenary, coaching, and facultative sessions is 16, 7, and 10 hours, respectively.

Throughout the entire program, participants can access the Voeding Leeft online platform to stimulate the implementation of healthier habits. At this platform, there are recipes for 30 days, and participants can also find more background information about all 4 pillars, ask questions (directed at the program coordinator, nutritionist, coach, or peers), chat with other participants to share their experiences and/or track their progress to ensure the implementation of a more lasting lifestyle behavior change.

Noteworthy is the fact that there will be no information exchange between the treating rheumatologist and the organization of the online, interactive lifestyle intervention program. However, for this trial, Voeding Leeft will record whether participants attend the plenary and coaching sessions and track their activity on the online platform.

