With the HELIA trial, we hope to prove that lifestyle interventions can be integrated into standard care for patients with IA alongside DMARD treatment. The program’s strength lies in its focus on multiple lifestyle domains—nutrition, exercise, relaxation, and sleep—with the aim of achieving lasting behavioral change (based on the I-Change model) [18]. The study design also includes several strong features, such as a randomization procedure and an extensive follow-up period after the lifestyle intervention. The online, interactive lifestyle intervention, organized by Voeding Leeft, has also shown success in other patient groups, including the Reverse Diabetes 2 program [19]. We hope that the results of this study will encourage policymakers and insurers to recognize lifestyle interventions as reimbursable components of IA care.

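### The last visit coincides with the end of the 24-month programme, so the trial can show maintenance while aftercare is offered but not permanent change or an effect after the programme

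*Protocol article*

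**What the plan says.** Under Online, Interactive Lifestyle Intervention Program, the allocated intervention "consists of a 6-month, intensive part followed by an 18-month online aftercare period". The abstract describes it in the same way. The text after Figure 1 says what the aftercare contains. "After the first 6 months, participants can participate in facultative sessions to stay motivated and foster the healthier habits", these sessions resemble the coaching sessions, and "A facultative session is organized every 9 weeks". On the platform it says: "Throughout the entire program, participants can access the Voeding Leeft online platform to stimulate the implementation of healthier habits".

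The visit schedule is under Participant Timeline: "Patients will be assessed at baseline and after 3, 6, 12, and 24 months". Table 2 has no later column. The Results section gives May 2024 for the end of recruitment and May 2026 for the last visit.

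Two statements rest on this schedule. Secondary End Points says "we will follow all participants for 2 years to determine the long-term effect of the lifestyle intervention" and to establish "whether the intervention has led to a permanent behavioral change". The Discussion, under Principal Findings, lists "an extensive follow-up period after the lifestyle intervention" among the strong features of the design.

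**The concern.** To claim permanence, or an effect after an intervention, a trial needs at least one observation made once the intervention has stopped. Here every post-baseline visit falls while the intervention arm is still inside its allocated programme. A favourable 24-month result reported in the current wording would be read as durability after the programme, when it would show maintenance with support still available.

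The distinction matters to the intended audience. Lasting behaviour change is the programme's stated aim, and the Discussion hopes the results will move policymakers and insurers towards reimbursement. Whether benefit outlasts the support is a question they may well ask, and these data do not answer it.

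**Working it through.** **Inputs**
- Intensive part: 6 months; aftercare: 18 months (Online, Interactive Lifestyle Intervention Program; abstract).
- Visits at months 0, 3, 6, 12 and 24 (Participant Timeline; Table 2).
- Recruitment completed May 2024; last visit May 2026 (Results).
- Contact hours: 16 plenary, 7 coaching, 10 facultative; one facultative session every 9 weeks (text after Figure 1).

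**1. The plan's own calendar.** May 2024 + 24 months = May 2026. The stated last-visit date is reproduced, and it leaves no measurement beyond month 24 for the last participant.

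**2. Follow-up after the whole programme.** Programme length = 6 + 18 = 24 months. If the programme starts at baseline, follow-up after it = 24 − 24 = 0 months, with 0 visits.

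**3. Sensitivity to the start date.** The article does not give the interval from baseline to programme start. Consent and eligibility checks are at T0, so the programme should not start earlier. With an assumed delay of *d* months, the programme ends at 24 + *d*:

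| Assumed delay (months) | Programme ends (month) | Last visit minus programme end (months) | Visits after the end |
|---|---|---|---|
| 0 | 24 | 0 | 0 |
| 1 | 25 | −1 | 0 |
| 3 | 27 | −3 | 0 |
| 6 | 30 | −6 | 0 |
| 7 | 31 | −7 | 0 |

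A delay only moves the last visit further inside the programme.

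**4. Follow-up after the intensive part alone.** 12 − 6 = 6 months and 24 − 6 = 18 months. Two visits follow it, both within the aftercare period.

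**5. How much support aftercare represents.** 18 months is about 78 weeks, and 78 / 9 = 8.7, so about 8 to 9 optional sessions. Their 10 hours are 10 / (16 + 7 + 10) = 10 / 33 = 30% of all scheduled contact hours. The intensity is much lower than before: (16 + 7) / 6 = 3.8 hours per month in the intensive part against 10 / 18 = 0.6 hours per month in aftercare. Support is light and optional, but it is on offer until about month 24.

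**The case against.** The strongest reply is that the real intervention is the intensive part. It carries 23 of the 33 contact hours in a quarter of the time, the aftercare is optional, and the adherence analysis is anchored at the end of the intensive part. On that view the 12- and 24-month visits are genuine follow-up, and behaviour held for 18 months with light, optional support says something about durability.

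Much of this stands. A reader might infer that nothing at all is measured after the intervention, or that the trial is silent on lasting change. The documents do not support that: two visits follow the intensive part, and maintenance with aftercare available is a meaningful result. It is also the relevant effect for anyone deciding on the 24-month package as delivered.

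The reply does not rescue the two statements, however. The article defines aftercare as a component of the programme, and where it means the first six months it names the intensive part explicitly (Strategies to Improve Adherence to Interventions; Additional Analyses).

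A reader might also infer that aftercare use goes unrecorded, because the sentence on attendance names only plenary and coaching sessions. That goes too far. The same sentence plans tracking of platform activity, and whether facultative attendance is logged is a detail that a condensed article may leave to the full protocol.

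Finally, permanent change is not among the numbered objectives in the Introduction, the behavioural measures are exploratory, and the list of strengths at the end of the article mentions only a long follow-up period, which is accurate. This limits the weight of the point but does not remove it.

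**Conclusion.** The point holds in a limited form. For the programme as the article defines it, scheduled follow-up after its end is 0 months and 0 visits. The trial therefore cannot establish permanent behavioural change and does not have the post-intervention follow-up that the Discussion claims. It can show maintenance to 24 months with aftercare on offer, 18 months after the intensive part.

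This rests on two assumptions: that the programme starts at or after baseline, and that visits take place on schedule. It would be too strong to say that the 24-month visit falls on the programme's last day, because the start interval is not given; any delay places the visit before the end.

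No estimator, analysis set, sample size or primary result changes. The correction concerns one stated aim, one claimed strength and how the 24-month results are interpreted. It should be made before reporting.

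**What to change.** 1. In Secondary End Points, restate the purpose of the second year as *maintenance of effect and behaviour up to 24 months, while optional aftercare is offered*, and drop the reference to permanence.
2. In the Discussion, under Principal Findings, restate the claimed strength in the same terms.
3. Limit conclusions from the 24-month visit accordingly.
4. Aftercare use (the platform activity already tracked, and facultative attendance if it was recorded) may be reported descriptively as exposure in the intervention arm. It should not be presented as showing whether continued support carries the effect. Attendance is chosen by participants after randomisation and exists in one arm only, so motivated or better-responding patients may attend more.

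The cost is wording and a more modest claim. Attendance at sessions already held cannot be recovered unless records exist, so item 4 depends on what was kept. Keeping the stronger claims would instead require a measurement after aftercare ends, which the present schedule does not contain.

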### Exploratory End Points

Exploratory end points include self-reported disease activity (states), sleep, perceived stress, physical activity, and diet compliance (refer to Table S1 in Multimedia Appendix 1). Self-reported disease activity is measured with the Routine Assessment of Patient Index Data 3 (RAPID-3) [47]. Thresholds for remission and moderate-to-high disease activity are respectively <3.1 and ≥6.1 on a 0‐30 scale. The MCID for the RAPID-3 is 3.8 [48].

The quality of sleep is measured with the Medical Outcomes Study sleep scale (MOS-SS) [49]. The MOS-SS includes 12 items assessing sleep disturbance, sleep adequacy, somnolence, quantity of sleep, snoring, and awakening. A sleep problems index, grouping items from each of the former domains, is also available. The MCID for the sleep problem index is ≥6 [50].

Perceived stress is measured with the Perceived Stress Scale (PSS-10) [51]. The PSS-10 consists of 10 items, and items are scored on a 0‐4 response scale. Higher scores represent higher levels of stress. The MCID of perceived stress is ≥11 [52].

Physical activity is measured with the Dutch Physical Activity Guideline (Nederlandse Norm Gezond Bewegen [NNGB]) [53]. The NNGB measures whether an individual complies with the Dutch Guidelines for Physical Activity, and a higher score corresponds with better compliance.

Diet compliance is measured with a self-developed questionnaire consisting of 17 items based on the 17-item Mediterranean diet questionnaire [54]. Each dietary compliance item is scored as 1 if it aligns with the principles of the Mediterranean diet, and 0 otherwise. Total scores range from 0 to 17, with a score of 0 to 7 equating to a low dietary compliance, a score of 8 to 10 for an average degree of dietary compliance, and a score of 11 to 17 for a high degree of dietary compliance.

